#### Interim analyses {21b}

A Data Monitoring and Safety Board (DSMB), independent of the trial organisers and sponsors, has been established with the remit to review trial progress. The terms of reference for the DMSB were agreed upon at their first meeting and documented in the DSMB charter. The DSMB is chaired by a senior clinical trialist, and members include two statisticians and a clinician. Interim data analyses are supplied, in strict confidence, to the DSMB, as frequently as the chair requests and meetings are held at least annually. Based on interim data on the trial’s outcomes, adverse event data, accumulating evidence from other trials and any other relevant evidence, the DSMB will inform the Trial Steering Committee (TSC) if, in their view, there is proof beyond a reasonable doubt that the data indicate that any part of the protocol under investigation is either clearly indicated or contra-indicated, either for all trial participants or for a particular sub-group of trial participants. A difference of at least 3 standard errors in the interim analysis of a major endpoint may be needed to justify halting, or modifying, such a study prematurely.

#### Methods for additional analyses (e.g. sub-group analyses) {20b}

Pre-specified sub-group analysis of factors known to be associated with infant cognitive development—maternal education, socio-economic class, the severity of depression at trial entry and infant sex—will be performed for the infant cognitive development outcome at 24 months using the statistical test of interaction. Sub-group analysis based on maternal education, socio-economic class and infant sex concerning maternal depression at 12 months will also be performed. The sub-groups will be categorised as follows:
Maternal education (primary completed or below; grade 10; matriculation or above).Socio-economic status (paid employment yes/no).Severity of depression at trial entry (continuous).Infant sex (male/female).

#### Methods in analysis to handle protocol non-adherence and any statistical methods to handle missing data {20c}

Women with outcome data will be analysed in the groups to which they are randomly assigned, regardless of deviation from the protocol or treatment received (modified ITT population). Women whose infant died during the trial will also be included unless they withdrew consent to participate further in the trial.

The number and percentage of individuals missing data for outcome measurements that are based on summing items to give overall scores (e.g. EPDS, GAD-7, and subscales of the PSI/SF and CBCL) will be described. Missing items will be imputed if ≤ 20% are missing using the median score of completed scale items unless alternative guidance is provided in the scoring manual.

A multiple imputation analysis will be performed for the primary infant and maternal outcome if attrition exceeds 5%. The multiple imputation model will include baseline characteristics and outcome measures collected before the missing assessment, which are associated with missing status.

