#### Sample size {14}

The first primary outcome is the cognitive subscale on the BSID-III at 24 months of age. To achieve power of over 90% (two-sided *t*-test with a significance level of 0.05), and assuming an estimated difference of 6 points (SD 15), a total sample size of 396 women (198 per arm) is required. This calculation takes into account geospatial clustering (28 clusters per arm with an intra-cluster correlation coefficient (ICC) of 0.05) and ‘counsellor effect’ in the intervention arm (4 lay counsellors with an ICC of 0.05). To take account of attrition of up to 25%, a total sample size of 528 women is being recruited (264 per arm, 48–60 geospatial clusters, 9–11 women per cluster).

Using the EPDS assessment with a standard deviation of 5, with the same assumptions of clustering as above, a difference of 2 points between trial arms (not adjusting for baseline or repeated measurements) could be detected with 90% power and a 5% two-sided significance level. Analysis using repeated measures, taking into account within-participant correlation over time, would allow smaller differences to be detected with the same power

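### The multiple-imputation rule picks predictors by their link with missingness and only from earlier visits, so it does not call for strong outcome predictors or the 24-month EPDS

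*Protocol article*

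**What the plan says.** The missing-data section of the protocol article ({20c}) states when imputation is done: "A multiple imputation analysis will be performed for the primary infant and maternal outcome if attrition exceeds 5" per cent. It then gives the rule for building the model: "The multiple imputation model will include baseline characteristics and outcome measures collected before the missing assessment, which are associated with missing status".

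The same section defines the modified intention-to-treat population: "Women with outcome data will be analysed in the groups to which they are randomly assigned". It adds: "Women whose infant died during the trial will also be included unless they withdrew consent to participate further in the trial".

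Three other sections bear on this:

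- **Statistical methods ({20a}).** The EPDS is modelled as repeated measures at baseline, end of pregnancy, 12 months and 24 months. Geospatial cluster and counsellor are random effects. Primary inference rests on the adjusted mixed model, justified under missing at random.
- **Additional analyses ({20b}).** Maternal education, socio-economic class, severity of depression at entry and infant sex are named as factors known to be related to infant cognitive development.
- **Sample size ({14}).** "To take account of attrition of up to 25%, a total sample size of 528 women is being recruited".

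**The concern.** An imputation model gains from two kinds of variable. Those related to both the outcome and the missingness remove bias. Those related to the outcome alone add precision. A variable related only to missingness does neither. The stated rule screens on missingness and does not mention the outcome, so it can admit variables that do nothing and does not call for variables that would help.

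The timing limit is a separate matter. A woman who misses the 12-month visit but returns at 24 months supplies an EPDS score that should say a good deal about the missing one. The repeated-measures model uses that score; the imputation rule leaves it out. If the two analyses then disagree, the reader cannot tell whether the data are sensitive to the missing-data assumption or whether the imputation simply used different information.

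The article names no other missing-data analysis of the primary outcomes beyond the adjusted mixed model, and it is likely to be run: the trigger is 5% and the trial allows for up to 25%.

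**Working it through.** **1. The plan's own figure.** Evaluable sample 396, attrition 25%: 396 / (1 − 0.25) = 528. This agrees with the article, and no stated number is in dispute. The trigger of more than 5% of 528 is 0.05 × 528 = 26.4, so 27 losses are enough. The planning ceiling is 0.25 × 528 = 132.

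**2. Selection by missingness.** Of the four factors that {20b} names as related to cognitive development, the rule in {20c} calls for one only if it also turns out to be associated with missing status. Their known relation to the outcome does not count.

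The cost can be bounded. Suppose a fraction m of outcomes is missing and a further predictor has correlation r with the outcome, given what is already in the model. Without other predictors, the variance of an arm mean that uses it, relative to one that does not, is about

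(1 − r²) + r²(1 − m) = 1 − m·r².

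The reduction forgone is therefore at most about m·r². The documents give no r, so 0.3 to 0.6 is an assumed range:

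| m | r = 0.3 | r = 0.6 |
|---|---|---|
| 5% | 0.05 × 0.09 = 0.45% | 0.05 × 0.36 = 1.8% |
| 25% | 0.25 × 0.09 = 2.25% | 0.25 × 0.36 = 9% |

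This ignores clustering. It is a ceiling, because a predictor already in the adjusted analysis model, or overlapping with other predictors, adds less.

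**3. The timing limit, by outcome.**

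- *EPDS at 12 months.* Table 4 shows EPDS at screening, end of pregnancy, 12 weeks, 12 months and 24 months. The imputation rule reaches the first three. The repeated-measures model in {20a} uses the 24-month score. (The imputation could draw on the 12-week score, which {20a} does not list; that only widens the mismatch.) One analysis conditions on history before the gap, the other on scores from both sides of it, so the missing-at-random assumptions are not the same. The gain from the 24-month score is limited to women who miss 12 months and return at 24. The article does not give their number.
- *BSID-III at 24 months.* No later visit exists. The limit removes only measures taken at the same visit, such as the language scale, which would usually be missing together with the cognitive score. Little is lost here.

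**4. Allocation, conditional on omission.** The article does not state whether allocation is in the imputation model. If it were left out and earlier measures carried none of the effect, imputed values would show no difference between arms, so the expected estimate is (1 − m) × effect + m × 0:

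| m | BSID-III, 6 × (1 − m) | EPDS, 2 × (1 − m) |
|---|---|---|
| 5% | 5.7 | 1.9 |
| 10% | 5.4 | 1.8 |
| 25% | 4.5 | 1.5 |

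The 6 points (SD 15) and the 2 points are the effects assumed in {14}. A simulation for BSID-III used 264 women per arm, 28 clusters per arm, ICC 0.05, outcomes missing completely at random, 5 imputations and 400 runs. At 25% missing the mean estimate was 4.4 to 4.8 without allocation, depending on how the earlier measure was related to outcome and treatment effect, and 5.8 to 6.1 with it. With allocation included there is no attenuation.

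The effect of omitting clusters was not quantified. The number of infant deaths is not given, so that part cannot be sized.

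**The case against.** The strongest reply is that the sentence lists what the model will contain and never says that it contains nothing else. A journal article condenses the plan. Terms of the analysis model are ordinarily carried into the imputation model, and the article says that a statistical analysis plan will be available. This stands in full for two stronger readings that a reader might draw:

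- *That imputation omits allocation and clusters and so shrinks the effect.* The article is silent on both. Silence in a condensed account is not exclusion, and the attenuation figures describe a model that the article does not state.
- *That BSID-III scores would be imputed for children who died.* The sentence on infant death keeps the women in the population, which makes sense for the EPDS because the mother can still be assessed. Nothing says that a dead child's score is filled in, and nothing says that it is not. This calls for a clarification; it is not an error.

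Three further replies carry weight. Omitting an outcome predictor unrelated to drop-out costs precision and introduces no bias. The 25% is a ceiling for planning, and the retention section reports high retention in earlier trials in this community. The clause on missing status could also be read as qualifying only the earlier outcome measures; baseline factors would then enter without the screen, and the precision point would shrink.

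What does not fall is the rule itself. The article chose to fix a selection criterion and a time limit. The criterion is not the one that best serves imputation, and the limit departs from the trial's own model for the 12-month EPDS. Both are stated, so neither is a gap left for another document to fill.

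**Conclusion.** The point holds in a limited form. As written, the rule does not call for strong outcome predictors unrelated to drop-out, and it leaves out the 24-month EPDS when the 12-month EPDS is imputed. The first costs precision: at most about 2% to 9% of variance at 25% missing and under 2% at 5%, on assumed correlations of 0.3 to 0.6. The second makes the imputation differ from the repeated-measures model in information and in its missing-at-random assumption. Its size depends on how many women miss 12 months and return at 24, which is not known.

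The consequence stays within the supplementary imputation analysis. Primary inference rests on the adjusted mixed model and is not affected. The fall from 6 to 5.7 or 4.5 points applies only if allocation were in fact omitted, and should not be read as a property of the plan. This is a free improvement, not a flaw that threatens the trial's conclusions.

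**What to change.** Replace the predictor rule with one along these lines: *the imputation model includes variables associated with the outcome or with missingness, including outcome measures from any visit (for example the 24-month EPDS for a missing 12-month EPDS), together with all terms of the analysis model: allocation, geospatial cluster, counsellor and the adjustment covariates.*

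Naming the analysis-model terms removes any doubt about allocation and clustering. Add one sentence confirming that BSID-III is not imputed for children who died before 24 months, and report deaths by arm beside the result.

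The cost is wording in the protocol or statistical analysis plan and slightly more analysis work. No extra data are collected, and neither the sample size nor the primary analysis changes.

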#### Plans to give access to the full protocol, participant level-data and statistical code {31c}

Data will be available beginning 9 months and ending 36 months following main article publication to researchers who provide a methodologically sound proposal that purposes to achieve aims in the approved proposal and /or for individual participant data meta-analysis. Data is documented and stored on the AHRI Data Repository (https://data.ahri.org) with a digital object identifier (doi) and can be accessed with permission and in line with AHRI policies and procedures. Data requestors will need to sign a data access agreement before any data can be shared. In addition, Study Protocol and Statistical Analysis Plan documents will be available. Data sets associated with publications will be made available in line with Wellcome Trust data policies and journal requirements.

### Oversight and monitoring

#### Composition of the coordinating centre and trial steering committee {5d}

This trial is managed and coordinated by a trial group (management, operational and data management sub-groups) with regular advice and consultation from the investigators’ group and the AHRI Clinical Research Department.

The trial group composes of management, operational and data management sub-groups. The management sub-group consists of the principal investigators, trial manager, trial coordinator, and trial psychologist. The group meets at least once a week virtually to discuss and manage major trial operational challenges (screening, recruitment, assessments, therapy/ESoC), logistics, adverse events (AE) and severe adverse events (SAEs), staffing, and trial reporting and monitoring. Trial reporting and monitoring includes the management and reporting of AEs and SAEs and trial progress using summary statistics and graphs**.** The operational sub-group includes the four trial components (recruitment, assessment, therapy, ESoC) and is managed by the trial coordinator. The operational teams meet at least once a week, with individual meetings and contact points as needed. The four teams are operated separately to ensure blinding. The data management subgroup meets weekly and includes the AHRI data manager, trial manager and trial coordinator.

The investigators’ group consist of the trial management group and experts (investigators) in maternal health and early child development. The investigators are consulted regularly dependent on their specific roles and small sub-group meetings are organised as needs be. The whole group meets formally every 3 months. Trial Progress Reports containing updates, summary statistics and graphs and discussion points are submitted for these meetings.

The trial group confers regularly with the AHRI Clinical Research Department, primarily regarding SAE and AE management. The trial coordinator has frequent meetings with the head of the Clinical Research Department and attends regular AHRI wide project coordination meetings to ensure that the trial implementation is coordinated with awareness of other research activities in the study community.

The Trial Steering Committee (TSC) acts as the oversight body for this trial on behalf of the Sponsor/Funder and it should also provide advice through its independent Chair on all aspects of the trial. All substantial issues regarding the trial must go to the TSC for consideration. The Data Safety Monitoring (DSMB) is advisory to the TSC and the DSMB makes recommendations to the TSC based on the interim data. The TSC oversees the timely analysis, writing up and publication of the main trial results. The independent members of the TSC will have the opportunity to read and comment on the proposed main publications of trial data before submission. The TSC is made up of the chair, three independent members, including an experienced trials statistician. The TSC meets with the trial management team and an independent observer from the funding body at least annually and ad hoc as required to discuss trial issues.

#### Composition of the data monitoring committee, its role and reporting structure {21a}

The Data Monitoring and Safety Board (DSMB) consists of a chair (senior clinical trialist), two statisticians and a clinician. Interim data analyses are supplied, in strict confidence, to the DSMB, as frequently as the chair requests and meetings are held at least annually. The DSMB is independent of the trial organisers and sponsors. The terms of reference for the DMSB were agreed upon at their first meeting and documented in the DSMB charter. Based on interim data on the trial’s outcomes, adverse event data, accumulating evidence from other trials and any other relevant evidence, the DSMB will inform the Trial Steering Committee (TSC) if, in their view, there is proof beyond a reasonable doubt that the data indicate that any part of the protocol under investigation is either clearly indicated or contra-indicated, either for all trial participants or for a particular sub-group of trial participants. A difference of at least 3 standard errors in the interim analysis of a major endpoint may be needed to justify halting, or modifying, such a study prematurely.

#### Adverse event reporting and harms {22}

The processes of risk identification and management have been developed and tested. The trial has, in collaboration with the AHRI Clinical Research Department, identified and established referral pathways for the management of risk, including referrals to the local DoH and DSD services. The AHRI Clinical Research Department assists with the management of medical SAEs. We have developed a protocol for the management of these events and reporting at appropriate times to the DSMB.

The trial distinguishes between severe adverse events (SAEs) and adverse events (AEs). SAEs pose a high risk to the mother and/or enrolled child and require urgent attention and management. SAEs include maternal/child death; physical illness requiring hospitalisation ≥ 5 days; severe psychological or psychiatric illness (may require hospitalisation; current suicidal ideation with intention and/or a plan; self-harm; serious social harm (e.g. interpersonal violence-causing immediate danger or risk); stigma, emotional harm or risk of displacement/insecure housing (as a direct result of trial participation); and inadvertent disclosure of participants HIV status or breach of confidentiality (intentionally or unintentionally by research staff). Details of the SAE and a brief management plan are communicated to the DSMB Chair within 24 h of the team being notified of the SAE. Furthermore, SAEs are reported to the HSRC and OxTREC ethics committees within 7 days of the team being notified of the SAE.

In contrast, AEs are defined as events that do not pose an immediate risk to the mother/infant but require management and attention to prevent escalation into a high-risk event (SAE). These include relationship problems/conflicts, feelings of hopelessness and suicidal thoughts without serious intent or plans. These are monitored and recorded and reported to the ethics committees and the DSMB as AEs.

Additional information about the management of risk cases is documented under ‘Enhanced Standard of Care’ on page 23.

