**Methods:**

This study is a cluster randomised controlled trial, consisting of 48–60 geospatial clusters. A total of 528 pregnant HIV-positive women aged ≥ 16 years who meet the criteria for depression on the Edinburgh Postnatal Depression Scale (EPDS, score ≥ 9)) are recruited from antenatal clinics in rural KwaZulu-Natal, South Africa. The geospatial clusters are randomised on an allocation ratio of 1:1 to either the intervention or Enhanced Standard of Care (ESoC). The intervention group receives 10 home-based counselling sessions by a lay counsellor (4 antenatal and 6 postnatal sessions) and a booster session at 16 months. The intervention combines behavioural activation for depression with a parenting programme, adapted from the UNICEF/WHO Care for Child Development programme. The ESoC group receives two antenatal and two postnatal counselling support and advice telephone calls.

In addition, measures have been taken to enhance the routine standard of care.

The co-primary outcomes are child cognitive development at 24 months assessed on the cognitive subscale of the Bayley Scales of Infant Development-Third Edition and maternal depression at 12 months measured by the EPDS.

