##### Session structure

The combined intervention is delivered by lay counsellors in the participants’ homes across 10 sessions, starting in pregnancy (between 26 and  36 weeks of gestation) through to 9 months postnatal, along with an additional booster session at 16 months postnatal. The initial session lasts up to 2 h and focuses on orientation to BA and assessment of behaviours around depression using a BA diagram to conceptualise problem behaviours. The session focuses on BA only. The remaining sessions last approximately 1.5 h each, compromising combined mother-focused BA modules and infant-focused parenting components. The therapy arm also receives a ‘keep in contact call’ at 36–38 weeks of gestation between therapy session 4 and delivery.

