##### Enhanced Standard of Care (ESoC)

In addition to the standard of care in the district, the ESoC arm receives a telephonic counselling support and advice intervention which also ensures referrals and access to care where necessary. The counselling support intervention includes four support and advice phone calls. The ESoC call programme was informed by the enhanced care package used in a recent perinatal depression trial in South Africa [57].

The telephone counselling uses questions, guided by standardised scripts, and supportive listening to enable the caller to assess the participant’s current emotional wellbeing and health, and to ensure referrals and access to care where necessary. The caller (who has had at least 2 years of counselling experience) provides advice and supports problem-solving around managing their mental and physical health as well as partner and family relationships. Scripts for each call have been developed to support the caller in dealing with these issues. The caller also guides participants to use the services and support provided by the district DoH services. Training and supervision support the ESoC caller to be empathic and responsive to the participants. The caller also identifies risk situations, including suicidal ideation, that have arisen. The caller reports and refers these to the trial risk management team in line with the trial risk management protocol for further action. ESoC participants receive all four support calls from the same support caller. The participants are also provided with a study telephone contact number in case of urgent need and are given telephone credit.

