In addition to the phone calls provided to the ESoC arm, participants are assessed on 7 occasions as part of the trial (baseline and six follow-up assessments) (both arms) by trained assessors which enables the identification of problems of significant clinical risk or concern. When these arise, they are evaluated by the team which includes a full-time on-site clinical psychologist. This is followed by initial management and onward referral to medical, psychological, and social services depending on the case. Psychological cases are managed by the trial risk management team and the AHRI Clinical Research Department. An initial assessment is always provided by the trial clinical psychologist. Where appropriate, the psychologist undertakes initial management and follow-up to ensure timely assessment and care without overburdening the local DoH services. The trial psychologist liaises with and makes referrals to the local DoH psychologist and the Department of Social Development (DSD) (social services) as necessary. Support for medical and social cases is provided by the AHRI Clinical Research Department. In collaboration with this department, the trial has established referral pathways and working relationships to the local DoH and DSD. In addition, all referrals are actively monitored until care has been accessed and, where necessary, the trial team continues to follow up.

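### Disclosure-dependent adverse events surface largely at trial contacts, which are unequal by design (18 versus 10 after randomisation), so event counts by arm can differ with no true difference in harm

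*Protocol article*

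**What the plan says.** The section on adverse event reporting and harms {22} separates SAEs from AEs. The SAEs include death, hospital stays of at least 5 days, suicidal ideation with intention or a plan, self-harm, serious social harm such as interpersonal violence, and disclosure of HIV status. The AEs include relationship problems and "feelings of hopelessness and suicidal thoughts without serious intent or plans". Of the AEs it says: "These are monitored and recorded and reported to the ethics committees and the DSMB as AEs". SAEs are reported from the time the team is notified. Neither definition depends on who noticed the event or at which contact.

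For the management of risk cases that section refers to the ESoC section, which names two detection routes. One is common to both arms: "participants are assessed on 7 occasions as part of the trial (baseline and six follow-up assessments) (both arms) by trained assessors", and these assessments are said to bring problems of clinical risk to light. The other belongs to ESoC alone: "The caller also identifies risk situations, including suicidal ideation, that have arisen".

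Contact outside the assessments differs by arm. The abstract says: "The intervention group receives 10 home-based counselling sessions by a lay counsellor (4 antenatal and 6 postnatal sessions) and a booster session at 16 months". Under session structure, the article adds a keep-in-contact call "at 36–38 weeks of gestation between therapy session 4 and delivery" and gives the length of visits after a first session of up to 2 h: "The remaining sessions last approximately 1.5 h each". ESoC has two antenatal and two postnatal calls, the last at 4 months.

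The DSMB advises the steering committee on whether any part of the protocol is clearly indicated or contra-indicated. Its basis is stated as: "Based on interim data on the trial’s outcomes, adverse event data, accumulating evidence from other trials and any other relevant evidence".

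**The concern.** Most of the listed AEs, and some SAEs (suicidal ideation with a plan, violence), leave no record unless the woman discloses them. The chance that such an event is counted therefore depends on how often, for how long and in what setting someone from the trial talks to her. Here that is part of the randomised treatment. One arm gets repeated home visits into the first year and a booster in the second. The other gets four scripted calls that end at 4 months postnatal.

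Some of these states may also be present at entry. All women have an EPDS score of 9 or more. The exclusion criteria remove only suicidal ideation with specific plans and means, so a woman with suicidal thoughts but no plan can be enrolled, and that state is itself a listed AE. The AE definition has no condition that the state be new or worse.

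What is at stake is how harms data are read. A higher count in the intervention arm might be surveillance, and equal counts might hide a real difference. Both the DSMB and any final harms report would face this ambiguity.

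**Working it through.** **1. Reproduce the stated count.** The ESoC section gives 7 assessments. Table 4 lists A1 to A7, and the data collection section lists six after baseline: end of pregnancy, 6 days, 12 weeks, 6, 12 and 24 months. Baseline precedes randomisation, so 7 − 1 = 6 common assessments follow it.

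**2. Scheduled contacts after randomisation.**

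| | Intervention | ESoC |
|---|---|---|
| Common assessments | 6 | 6 |
| Sessions or calls | 10 | 4 |
| Booster | 1 | 0 |
| Keep-in-contact call | 1 | 0 |
| Total | 18 | 10 |
| Arm-specific | 12 | 4 |

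Ratio: 18/10 = 1.80. Other fair counts are 17/10 = 1.70 without the keep-in-contact call, 19/11 = 1.73 with baseline included, and 18/11 = 1.64 with baseline and without the call. Arm-specific contacts alone give 12/4 = 3.0.

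**3. From contacts to recorded events.** Let a, t and e be the relative sensitivity of an assessment, an intervention contact and an ESoC call. With equal true harm, and events found in proportion to contacts, the expected ratio (intervention to ESoC) is (6a + 12t)/(6a + 4e). The article gives none of these sensitivities. Assumed values show the range:

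| Assumption | Ratio |
|---|---|
| All contacts equal | 18/10 = 1.80 |
| t and e half of a | 12/8 = 1.50 |
| t and e a quarter of a | 9/7 = 1.29 |
| e = a, t one third of a | 10/10 = 1.00 |
| e = a, t = 0 | 6/10 = 0.60 |
| a = 0, t = e | 12/4 = 3.00 |

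**4. Scale in women affected.** Assume all contacts are equally sensitive, with a chance p per contact that an AE is recorded. The chance of at least one recorded AE is 1 − (1 − p)^k, with k = 18 or 10. For p = 0.01 this gives 16.5% versus 9.6%; for p = 0.02, 30.5% versus 18.3%; for p = 0.05, 60.3% versus 40.1%. All of these arise with no true difference. The values of p are illustrative.

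**5. Which events.** Deaths and hospital stays of 5 days or more should come to light through tracing and follow-up whatever the contact schedule, so the ratio for them should be near 1. The problem lies with events that depend on disclosure.

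**6. Comparable measurement already in the schedule.** All six post-baseline assessments are common: 6/6 = 1.00. Table 4 schedules the EPDS at four of them (end of pregnancy, 12 weeks, 12 and 24 months), and also at screening. So suicidality can be compared 4 versus 4 on the same item, relative to an entry value.

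**The case against.** The strongest reply has four parts.

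- The article describes no between-arm test of AEs and does not say that events are pooled over sources. Ascertainment rules and report tables would normally sit in the DSMB charter and the risk management protocol, which are cited but not shown. This stands in part: a rule may exist there. But the article itself fixes the contact schedule, the event definitions and the DSMB's use of adverse event data, and these together create the ambiguity.
- Only assessors and the ESoC caller are expressly said to identify risk. Detection by intervention counsellors is an inference. This is correct, though the inference is strong: the counsellors are supervised weekly by the trial psychologist, who makes the initial assessment of psychological risk cases and belongs to the group that manages AEs and SAEs. It does mean that the direction is open, as the 0.60 line shows.
- AEs are defined as events that need management, so not every symptom is logged. This also stands. Symptoms present at entry can inflate counts, but nothing shows that each contact logs them.
- Unscheduled routes exist, such as the telephone number given to ESoC women for urgent need. They could narrow the gap by an unknown amount.

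A reader might infer that AEs will be inflated against the intervention by up to 1.8 times. The article does not support this: 1.8 is a ratio of contacts, and as a ratio of events it is neither a bound nor of certain sign. A reader might also infer that such an artefact could reach the 3 standard errors named for halting. That figure is stated for a major endpoint, as something that may be needed, and is not a trigger for AEs. No AE counts are given from which a standardised difference could be calculated.

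**Conclusion.** The point holds in limited form. Scheduled opportunity to detect disclosure-dependent events is 18 versus 10 contacts after randomisation (1.64 to 1.80 under different fair counts), and 12 versus 4 for arm-specific contacts. Counts by arm can therefore differ without any difference in harm. The size and direction rest on sensitivities per contact that the article does not give; the assumed cases above run from 0.6 to 3.0. The conclusion needs only that contact types differ in number and may differ in sensitivity, and that the DSMB sees events by arm. It does not extend to deaths and long admissions, does not show that the intervention arm will look worse, and does not touch the primary outcomes. If the DSMB charter or the risk management protocol already separates events by source, the remaining step is to say so.

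**What to change.** Record the detection source of every AE and SAE (common assessment, therapy session, ESoC call, other), and show harms by arm stratified by source in DSMB reports and in the final report.

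- Keep all SAEs from every source in the by-arm table, including violence, self-harm, HIV-status disclosure and confidentiality breaches. Home visits could themselves cause some of these, so restricting the table to the common assessments could hide true harm.
- For suicidality, base the between-arm comparison on the EPDS self-harm item at end of pregnancy, 12 weeks, 12 months and 24 months, relative to the screening value.
- For other disclosure-dependent AEs, treat those found at the common blinded assessments as the comparable set, and describe session- or call-detected AEs without a comparative claim.

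Reporting and management of every event stay as they are. The cost is one source field, or coding from the session checklists, call records and referral records that the article says are kept, plus revised report tables. Recruitment closed in July 2021, so 24-month assessments were still ahead for the last women enrolled when the article appeared. The downside is fewer events in the comparative AE table. The EPDS also covers only the previous 7 days, so it misses episodes between assessments, though on the same schedule in both arms.
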